**Methods/Design:**

The longitudinal, mixed-method study examines key psychosocial variables related to the acquisition and to the long-term maintenance of skin self-examination in 200 patients with melanoma. Practice of self-exam behaviors is assessed at 3 and 12 months after receiving an educational intervention designed based on best-practice standards. Examined predictors of skin self-exam behaviors include biological sex, perceived self-exam efficacy, distress, partner and physician support, and coping strategies. Qualitative analyses of semi-structured interviews will complement and enlighten the quantitative findings.

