### Study objectives

The main objective of this study is to identify short- and long-term predictors of SSE after providing best-practice clinical care, which includes medical advice on SSE, and to better understand challenges and opportunities for secondary prevention of melanoma in high-risk individuals. Specific objectives include:

(1) To determine the extent of thorough SSE performance, defined in terms of completeness and frequency, at 3 months (i.e., Endpoint 1) and at 12 months (i.e., Endpoint 2) after receiving a standardized dermatological education session on SSE during melanoma follow-up care.

(2) To identify psychosocial variables, including distress, coping strategies, and physician and partner support that are independently associated with thorough SSE at 3 months and at 12 months following a standardized dermatological education session.

(3) To use qualitative methods to understand psychosocial factors, including physician and spousal support of SSE (or lack thereof), that help patients to affectively, cognitively and behaviorally adjust to the melanoma diagnosis and to the continuous need for SSE.

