### Hypotheses

1. The prevalence of thorough SSE will be higher during the first 3 months than during month 9 to 12 after standardized dermatological education on SSE.

2. Sex will predict SSE in terms of frequency and completeness. Psychosocial variables, including partner and physician support, psychological distress and coping strategies, will significantly predict additional variance in SSE performance assessed at 3 months and at 12 months after standardized dermatological education on SSE.

3. Physician and spousal support of SSE will play an important role for the patient’s psychological adjustment to the melanoma diagnosis and to the continuous need for SSE.

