During regular clinic visits up to 12 months after their melanoma diagnosis, i.e., at time 1 (T1), eligible patients will be advised by the clinical care staff about the opportunity to participate in the study. In addition, the study will be advertised through flyers and posters in the waiting room area, which will allow interested patients to proactively contact the research team about study participation. The research assistant will provide study information to interested patients, verify study eligibility and collect written, informed consent. Participants will be asked to complete baseline questionnaires on sociodemographic and illness-related information, past SSE behaviors, and psychological functioning at the clinic. Alternatively participants can complete the questionnaires at home and return them to the research team by mail. The research assistant (RA) will access the participants’ medical charts in order to complete the medical information sheet. The second assessment will take place in conjunction with the delivery of the dermatological education at the clinic 3 to 6 months after T1, i.e., at time 2 (T2). Participants will complete questionnaires about distress, coping strategies, physician support and about SSE knowledge, attitude, and self-efficacy. In addition, participants who, at the time of data collection, report having a spouse (i.e., having a committed intimate relationship), will be asked to answer questions related to their partner’s impact on SSE practice. Furthermore, these patients will be asked to take home a survey for their spouse, which mirrors the partner-related questions that the patient is asked to answer regarding SSE. Also at time 2, all study participants will receive a 20-minute standardized dermatological education on SSE derived from empirical evidence [14,29,47,50,65,98-104] and best practice guidelines [36,38,105-109]. Patients will be encouraged to attend the education session together with a significant other (e.g., spouse, other family member, friend) who could assist them with SSE. During the education session, the dermatology-trained RA, i.e., the health educator, will emphasize the usefulness of monthly whole body exams as an effective measure to detect suspicious skin lesions as early as possible. The educator will provide detailed information about how to conduct an effective SSE. This will include an explanation of the well-established ABCDE paradigm (lesion Asymmetry; Border irregularity; Color variation; Diameter; Evolution, e.g. change in size, shape, symptoms, etc.) [110-113] for the detection and interpretation of pigmented lesions by lay persons and health care professionals. Furthermore, the educator will provide handouts, which will assist participants with regular SSE, including a summarizing brochure on melanoma [114], a bookmark with color printed examples of lesions [111], a leaflet providing the link to an online video modeling skin self-examination [115], and a SSE Journal to record skin spots of concern and body parts covered during each home SSE [116,117]. At the end of this 20-minute session, the educator will encourage the participant to reflect on their SSE intentions. Subsequently the participant will be asked to note down in the SSE journal *if*, *when*, *where*, and *assisted by whom* the participant plans to conduct self-exams. At time 3 (T3), i.e., 3 months after the dermatological education, participants are invited by letter to fill out questionnaires assessing distress, coping strategies, physician and spousal support as well as SSE knowledge, attitude, and self-efficacy. In addition, a 10-minute, structured SSE behavior interview with the RA will be scheduled for T3 to assess practice of SSE over the last 3 months. At time 4 (T4), 12 months after the dermatological education, participants will be invited by letter to complete an assessment identical to T3, i.e., questionnaires and SSE behavior interview. At T4 a subsample of 30 patients, which will include the first 15 men and the first 15 women who consent to participate, will be invited to take part in a 50-minute individual, semi-structured interview based on the McGill Illness Narrative Interview [118] focusing on the following questions: 1) how patients deal with the diagnosis and how they experience the illness; 2) their experience regarding SSE, including how they deal with the ongoing need for thorough SSEs and obstacles to SSE; 3) their experience of physician support of SSE, or lack thereof, and how they deal with it; and 4) their experience of partner support of SSE, or lack thereof, and what facilitates or hinders partner support and how they deal with it. Biological sex is considered explicitly given that previous melanoma research suggests that this is a key variable in relation to SSE [27,45,119-121]. Participants will be invited to share and report their thoughts, feelings, and behaviors in each of the 4 domains, which were selected based on their relevance to the cancer trajectory and their presumed significance for SSE practice.

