
### Measures

#### Descriptive and independent variables: predictors of skin self-examination

Study measures were selected based on their wide use in cancer research, on their psychometric properties, and on their direct relevance to the objectives of the project. They are used to assess descriptive and independent variables, which are expected to have an effect on SSE behaviors during the first 3 months (T1) and 12 months (T2) after dermatological education.

The Sociodemographic Information Form [67] includes questions about age, sex, education, having a spouse, socioeconomic status, and cancer diagnosis. With the Medical Information Sheet [30] the RA gathers data such as time since diagnosis, melanoma stage and depth, previous diagnosis of cancer, melanoma treatment and disease progression. The Skin Cancer Prevention Scale [122] captures whether patients performed SSE and have been advised by health care providers about SSE prior to their current melanoma diagnosis. The Skin Cancer Knowledge Scale, based on questionnaires by Hay et al. 2006 [65] and Manne et al. 2006 [45], assesses knowledge regarding melanoma risk, melanoma warning signs and SSE. The SSE Attitude Scale, an adaptation of Manne’s SSE Benefits and Barriers Scale [45], assesses perceptions of SSE importance, personal gain through SSE, and barriers to SSE. The SSE Self-Efficacy Scale, based on Weinstock et al. 2007 [123], captures an individual’s self-confidence in performing effective skin self-exams. The Physician SSE Support Scale [124] inquires about the perceived interest that the treating physician conveys regarding the patient’s practice of SSE. The Berlin Social Support Scale [125] assesses the patient’s perception of emotional, instrumental and informational illness support provided by their spouse (patient perception and partner perception). The Skin Cancer Index [126,127] is a self-report scale focusing on emotional, social and appearance-related concerns associated with skin cancer. The Patient Health Questionnaire, PHQ-4, [128] screens for symptoms of depression and anxiety. The COPE Inventory [129] inquires about an individual’s use of coping strategies, e.g., mental disengagement, behavioral disengagement, focus on and venting of emotions, use of instrumental social support, denial, humor, use of emotional social support, planning and others.

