### Data analysis

In all relevant cases, additional analyses, including interaction effects and subsample differences, will be examined. **Data analyses related to objective ****1**(i.e., determining the extent of thorough SSE performance defined in terms of frequency and completeness): Descriptive and inferential statistics will be employed to gain a differential picture of patients’ practice of SSE in terms of completeness and frequency at T3 and T4 for the total sample as well as for subsamples according to sex, age, having a partner, etc. **Data analyses related to objective ****2** (i.e., identifying psychosocial variables independently associated with thorough SSE): First, hierarchical multiple regressions will be performed with SSE completeness as dependent variable using T3 data, i.e., 3 months after standardized dermatological education. The independent variables described above will be entered block-wise, i.e., 1^st^ block: sex; 2^nd^: skin cancer knowledge, attitude toward SEE; 3^rd^: self-efficacy for performing SSE; 4^th^: skin cancer-specific distress measure; 5^th^: partner support and physician support; 6^th^: total score of the coping measure (note that analyses will be repeated with the individual coping subscales). Second, a multinomial regression will be conducted with the same predictor variables and SSE frequency (i.e., too low, ideal and too high frequency) as the dependent variable. The strategies described for T3 will be repeated using the data collected at T4, i.e., 12 months after the education session. With the projected sample size of N = 200, a minimal R^2^ increment of .08 will be detected with .79 power. The power for detecting a R^2^ increment of .09 will be .85. The variance explained by both blocks and individual variables will be examined. The two dependent variables are treated separately because they reflect different aspects of SSE practice. As a second step, they may also be clustered and the resulting composite measure of SSE behavior will serve as the dependent variable in regressions similar to the ones described above. **Data analyses related to objective ****3**(using qualitative methods for an in-depth understanding of psychosocial factors related to SSE): Data saturation in qualitative theme analysis, depending on the level of structure of the interview, is often achieved with a sample of 10–15 participants who are examined intensively, while larger samples typically add only minimal new data [131]. Consensual Qualitative Research [131-133] will be applied to the semi-structured interviews of 15 male and 15 female patients. This qualitative method is based on principles of grounded theory [134] and aims at developing a theory directly grounded in the phenomena under study. As a first step, the 2 independent sets of interviews will be theme analyzed to establish preliminary categorizations through open coding. To guide this, the following preliminary questions will be used: how do patients cognitively, affectively and behaviorally adjust to cancer diagnosis and treatment?; how and why do patients engage in or refrain from performing SSE?; how do they experience practicing SSE (e.g., does SSE evoke discomfort, does it trigger tumor fear, does it lead to a sense of safety and control?); in which ways do significant others support or undermine SSE practice?; do patients find it hard to ask significant others for help with SSE or do patients feel overwhelmed by a others’ motivation to help?; and in which ways are physicians experienced as helpful or as non-supportive? Axial coding will then be conducted by which open codes are reviewed and synthesized. As a final step, selective coding will be conducted in order to articulate theories derived from the data and establish the inter-relations between the constructs that were found. By definition, Consensual Qualitative Research is conducted independently by two raters, who then meet to discuss their coding until a consensus is reached. A third independent rater will be available to address disagreements. All proposals are then edited by an editor.

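### The objective 2 models leave out the past-SSE item collected at T1, so a marker of an earlier habit can appear as an independent predictor, and the results cannot support wording about acquisition of SSE

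*Protocol article*

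**What the plan says.** Protocol article, Participants and procedures: at T1 participants complete "baseline questionnaires on sociodemographic and illness-related information, past SSE behaviors, and psychological functioning at the clinic". Under Descriptive and independent variables, the Skin Cancer Prevention Scale "captures whether patients performed SSE and have been advised by health care providers about SSE prior to their current melanoma diagnosis". The protocol therefore holds a measure of earlier SSE and lists it among the candidate predictors.

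Data analysis, objective 2: "The independent variables described above will be entered block-wise, i.e., 1^st^ block: sex; 2^nd^: skin cancer knowledge, attitude toward SEE". Block 3 is self-efficacy, block 4 skin cancer-specific distress, block 5 partner and physician support, and block 6 the coping total. That makes eight terms, and past SSE is not one of them. For frequency, "a multinomial regression will be conducted with the same predictor variables". For month 12, "The strategies described for T3 will be repeated using the data collected at T4".

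The question set for these models is about level. Objective 2 seeks psychosocial variables "independently associated with thorough SSE at 3 months and at 12 months following a standardized dermatological education session", and hypothesis 2 says that they "will significantly predict additional variance in SSE performance assessed at 3 months and at 12 months". The Abstract goes further: the study "examines key psychosocial variables related to the acquisition and to the long-term maintenance of skin self-examination in 200 patients with melanoma". The Discussion goes further still. It expects to explain which psychosocial factors have an effect on acquiring and keeping up SSE, and to use this to tailor prevention and design an intervention program.

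**The concern.** The structured SSE interview takes place only at T3 and T4. With no term for SSE before the education session, the models cannot tell a patient who began after the session from one who was already doing it. If distress, support or coping differs between patients with and without an earlier habit, and the habit carries over to T3, that variable gains a coefficient even when it has no influence on what patients do after education.

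The knowledge, attitude and self-efficacy blocks come earlier and absorb part of this, but not all of it. What is at stake is interpretation: a variable that marks an existing habit could be taken as a target for getting patients to start SSE.

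**Working it through.** **1. Is past SSE in any model?** The block list is introduced as a complete specification (i.e., not e.g.). Sex, knowledge, attitude, self-efficacy, distress, partner support, physician support and coping make 8 terms. Past SSE is in none of them, and the frequency and T4 models inherit the list. The general sentence on additional interaction and subsample analyses does not name past SSE.

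**2. The plan's power figures.** The article gives .79 for an R² increment of .08 and .85 for .09 at N = 200. It does not give alpha or the number of tested terms. Noncentral F: f² = increment/(1 − R²), u = tested terms, v = residual df, λ = f²(u + v + 1). With alpha .05, R² of the full model equal to the increment, and u = 11:
- Increment .08: f² = .08/.92 = .0870, v = 188, λ = 17.4, power .7916.
- Increment .09: f² = .09/.91 = .0989, λ = 19.8, power .8521.

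Both match the article. The choice of 11 terms is an assumption made because it matches. Other inputs also come close (alpha .0125 with 5 terms gives .785 and .852), and the 8 listed terms give .848 and .898. Nothing below depends on this choice except the cost of the fix.

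**3. How large a false increment can arise?** All correlations here are assumptions, because the article gives none. Let P be SSE just before the session. X is a psychosocial variable correlating a with P, and Y is T3 SSE correlating b with P, with no direct effect of X on Y. Knowledge, attitude and self-efficacy correlate c₁, c₂, c₃ with P, and sex is unrelated. With S = Σ c²/(1 − c²), the R² of Y on these variables is b²·S/(1 + S).

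Middle case, a = .3, b = .5:
- Strong covariates (.3/.5/.5): S = .0989 + .3333 + .3333 = .7656, so S/(1 + S) = .4336. Adding X (.09/.91 = .0989) gives .8645 and .4637. False increment = .25 × (.4637 − .4336) = .0075.
- Weak covariates (.2/.3/.3): S = .0417 + .0989 + .0989 = .2395, giving .1932. With X, .3384 and .2528. False increment = .25 × .0596 = .0149.

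**4. How often is X declared significant?** Simulation with 5,000 runs per cell, N = 200, two-sided 5%, X tested after sex and the three scales. The T1 item is binary (30% yes, assumed) and correlates q with P. Each cell shows strong / weak covariates.

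| a, b | no T1 item | item, q = .4 | item, q = .7 | P itself |
|---|---|---|---|---|
| .2, .4 | 9.9 / 14.8% | 9.5 / 12.1% | 6.8 / 8.3% | 4.6 / 4.5% |
| .3, .5 | 24.0 / 41.3% | 22.1 / 33.8% | 13.3 / 18.5% | 4.3 / 5.3% |
| .4, .5 | 41.5 / 65.5% | 34.6 / 56.4% | 20.8 / 30.2% | 5.1 / 5.1% |
| .5, .6 | 79.5 / 95.3% | 71.9 / 90.7% | 48.1 / 63.4% | 5.1 / 5.4% |

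The last column is near 5% by construction. The T1 item always helps, but by little if it tracks pre-session SSE poorly.

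**5. Cost in power.** One added covariate, 11 tested terms: v = 187, λ = .0870 × 199 = 17.3, power .7889 (from .7916). For .09, .8498 (from .8521). If λ is kept at N·f², the .08 figure is .7914, so .7889 is the cautious one.

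**The case against.** The strongest reply is that the analysis fits the question it serves. Objective 2 and hypothesis 2 ask about SSE at 3 and 12 months, the outcome is adherence to advice, and a patient who carries on an old habit is adherent. That stands. A reader might infer that the omission invalidates the objective 2 regressions; the documents do not support this, because no objective or hypothesis asks about change from before the session.

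Second, adding the T1 item would not make the results evidence on acquisition. This also stands. The item covers SSE before diagnosis. Recruitment runs to 12 months after diagnosis and the session follows 3 to 6 months later, so the gap can reach 12 + 6 = 18 months, and the item is not on the outcome scale. A reader might infer that its absence is what blocks the acquisition claim and that entering it would restore the claim. It would not, so the wording has to change either way.

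Third, the size is assumed. It is a significance rate for a linear outcome, the false increment in the middle case (.0075 to .0149) is well below the plan's .08, and nothing was simulated for the three-category frequency outcome. The simulated position is that of distress; for a term entered after three more scales that also correlate with earlier SSE, such as coping, the rates fall to about 19% to 30% in the middle case. All of this is fair and limits what the rates can show. It does not remove the mechanism, since individual variables as well as blocks are to be examined.

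Fourth, the Discussion foresees testing any resulting program in a randomized trial, so a wrong target would meet a check before use. That softens the consequence.

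**Conclusion.** The concern holds in a limited form. The objective 2 models answer the stated question about SSE level. They omit a measure of past SSE that the study already collects, so a variable that only marks an earlier habit can appear as an independent predictor. They cannot support the acquisition wording in the Abstract and Discussion.

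The size is illustrative only. For a variable with no effect of its own, false significance lies between about 10% (weak correlations) and 95% (strong correlations, weak covariates), with 24% to 41% in the middle case. In that case a T1 item with q = .7 brings the rate to 13% to 19%, and one with q = .4 only to 22% to 34%. These figures assume the correlations shown, a linear and normal outcome, and a binary item with 30% yes. The omission itself and the mismatch with the acquisition wording need no assumption.

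**What to change.** - Enter the T1 past-SSE item with sex or directly after it, ahead of the psychosocial blocks, in the completeness and frequency models at T3 and at T4.
- Report each model with and without the item. Adjustment may remove effects that act through earlier SSE, so neither version alone is sufficient.
- State that the item covers SSE before diagnosis and therefore adjusts only partly for SSE just before the session.
- Describe the results as predictors of SSE level after education, and change the acquisition wording in the Abstract and Discussion accordingly.

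Cost: no new data; one degree of freedom in the completeness model and two parameters in the three-category frequency model; one extra model per outcome and time point. Power for an increment of .08 goes from .792 to .789 under the assumed 11 tested terms, which is negligible.

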## Method/Design

### Participants and procedures

Ethical approval of the study protocol was granted by the Institutional Review Board of the Faculty of Medicine, McGill University (reference no. A11-B39-11B). Eligible patients will include English- and French-speaking adult patients with a confirmed diagnosis of melanoma who seek services at McGill teaching hospitals. Together, these hospitals treat over 400 new melanoma patients annually [77,78]. Previous psychosocial studies with cancer populations at the same hospitals [30,79,80] and at other sites [81-92] reported participation rates between 57-86%, with a mean of 76%. Attrition rates range between 4% and 24% in psychosocial studies with an assessment up to 18 months after the treatment of patients with melanoma [56,93] or other cancers [67,82,83,94-97]. Enrollment will take place over 2 years and continue until 200 participants have completed the study. A sample of 200 participants provides sufficient statistical power for the analyses (for power estimates see section Data analysis). At all time points the questionnaires will be provided as paper-pencil versions. Participants will be asked up to 3 times to mail back questionnaires completed at home. Interviews will be conducted over the telephone.

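### Block 5 enters partner support, which patients without a spouse do not have, so under a standard fit the models from block 5 onward fall short of the N = 200 behind the stated power

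*Protocol article*

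**What the plan says.** - **Who enters.** Under Participants and procedures, eligible patients are "English- and French-speaking adult patients with a confirmed diagnosis of melanoma who seek services at McGill teaching hospitals". No partner is required. Enrolment is to "continue until 200 participants have completed the study".
- **Who answers the partner items.** In the T2 description in the same section, it is "participants who, at the time of data collection, report having a spouse (i.e., having a committed intimate relationship), will be asked to answer questions" about the partner's impact on self-examination. Under Measures, the Berlin Social Support Scale is described as covering "emotional, instrumental and informational illness support provided by their spouse (patient perception and partner perception".
- **What the model needs.** Under Data analysis, objective 2, block 5 of the hierarchical regression for completeness is "partner support and physician support". Block 6, the coping total, follows. The multinomial model for frequency takes the same predictors, and both analyses are repeated at T4.
- **Power.** The statement opens "With the projected sample size of N = 200" and says that an R² "increment of .08 will be detected with .79 power", with .85 for an increment of .09.
- **Partner status elsewhere.** Having a spouse is recorded on the Sociodemographic Information Form. Having a partner is a planned subsample split under objective 1.

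**The concern.** Partner support is an ordinary regressor in a model meant for all participants, yet for a patient without a spouse it has no value. It is undefined rather than missing, so imputation has no target. A standard fit drops any patient who lacks a value for a regressor.

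Two things are at stake. The first is whom the results describe. Objective 2 seeks variables independently associated with thorough self-examination in the patients who received the education session. If unpartnered patients leave the later models, the adjusted results for physician support, coping and every predictor in the final model apply to partnered patients only. The excluded group is not incidental: the Background links comfort with a partner's help to self-examination, and two of the five scored body areas are on the back of the body. The second is that these models do not have the sample size on which the power statement rests.

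**Working it through.** **1. Which models are affected.** The blocks list eight predictors: sex (1); knowledge and attitude (2); self-efficacy (1); distress (1); partner and physician support (2); coping total (1).

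| Step | Contains partner support? | Patients available under a standard fit |
|---|---|---|
| Blocks 1–4 | No | All, unless one common sample is imposed |
| Block 5 increment | Yes | Partnered only |
| Block 6 increment | Yes | Partnered only |
| Final model | Yes | Partnered only |

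An R² increment compares two nested models on the same cases. The block 5 increment therefore also needs its comparison model (blocks 1–4) refitted on partnered patients. The increments for blocks 1 to 4 can still be computed on everyone. The same holds for the multinomial model and at T4.

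**2. Reproducing the stated power.** For an increment ΔR² with u tested and p total predictors, the test is F with (u, N − p − 1) df and noncentrality λ = N × ΔR² / (1 − R²_full). The article gives neither alpha, nor u, nor the R² of earlier blocks, so the figure has no unique reproduction. With no earlier variance, ΔR² = .08 and N = 200, λ = 200 × .08/.92 = 17.39. Settings compared with the stated .79 and .85:

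- alpha .05, u = p = 11: .792 and .852
- alpha .025, u = p = 8: .771 and .838
- alpha .01, u = 4, p = 8: .802 and .866
- alpha .05, u = p = 8 (the eight listed predictors): .848 and .898

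The first three are close to the stated pair; the last is higher.

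**3. Power on the partnered subset.** The partnered share is not in the article. Assume 60–80%: 200 × .60 = 120 and 200 × .80 = 160. Then λ = 160 × .08/.92 = 13.91 and 120 × .08/.92 = 10.43. With alpha .05 and ΔR² = .08:

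| Test | N = 200 | N = 160 | N = 140 | N = 120 |
|---|---|---|---|---|
| Block 5 alone (u = 2, p = 8) | .968 | .921 | .880 | .822 |
| Distress, support, coping (u = 4, p = 8) | .928 | .852 | .793 | .716 |
| All eight listed (u = p = 8) | .848 | .736 | .661 | .574 |
| 11-df match to .79 (u = p = 11) | .792 | .665 | .587 | .500 |

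At an assumed 90% (N = 180), the 11-df figure is .734 and the 2-df figure .949. These figures concern the linear model for completeness. The multinomial model loses the same patients, but the article states no power for it.

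**The case against.** The strongest reply is that the article says nothing about complete-case analysis or about how partner support is coded. Coding a not-applicable predictor is a detail that a condensed article may leave to a fuller plan, and the variable needed, having a spouse, is already collected. Part of this stands: the loss of patients follows from a standard fit with no special coding, not from a stated exclusion. But the article does fix the block order, the predictors, both outcomes, both time points and the N. Those conflict with its own rule on who answers the partner items, so this is more than an omission.

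A reader might infer more than the text supports:

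- *That the whole analysis cannot use 200 patients, or that all six blocks shrink.* Blocks 1 to 4 precede partner support and can use everyone. Suitable coding would also keep everyone in the later models.
- *That partner status is otherwise used only for description.* Data analysis opens by promising interaction and subsample analyses wherever relevant, and objective 1 includes inferential statistics. That promise does not supply block 5 with a value for unpartnered patients.
- *That power certainly falls to about .50.* This needs a 60% partnered share and the 11-df reading, which is only one match to .79. The 2-df test of block 5 stays at .82 or above across the assumed range, and the 4-df test goes below .79 only near its lower end.
- *That unpartnered patients are left out of the study.* They remain in objective 1. Help from significant others other than a spouse is recorded in the behavior interview, and a relative or friend may attend the education session.

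**Conclusion.** The conflict is real and limited in scope. Eligibility, the rule for the partner items and block 5 cannot all hold with N = 200 in the models that contain partner support, unless a coding is added that the article does not state. Without it, the block 5 and 6 increments and the final models, for both outcomes and both time points, describe partnered patients only.

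The restriction on whom the results describe holds whenever some participants have no spouse, as the planned split by having a partner expects. The size of the power loss is less certain: it rests on the assumed 60–80% partnered share, and on which test the stated power refers to. It is modest for block 5 alone (.97 to .82–.92), larger for the 4-df test (.93 to .72–.85), and largest for an 11-df test consistent with the stated power (.79 to .50–.67).

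**What to change.** Before analysis, fix the coding for patients without a spouse:

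1. Add a has-partner indicator, defined by the same report that decides who receives the partner items.
2. Enter partner support as indicator × (score − mean score of partnered patients), which is zero for unpartnered patients. All patients then contribute to the other coefficients. The indicator compares unpartnered patients with partnered patients at average support, and the product term gives the effect of support among the partnered.
3. Say whether the indicator enters before block 5 or within it. Within it, the increment has 3 df and mixes having a partner with the support received.
4. Use the same coding in the multinomial model and at T4.
5. State that the partner-support coefficient rests on the partnered subset, give its power for that N, and name the alpha and degrees of freedom behind the .79 and .85.

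The coding assumes that the other coefficients are the same with and without a partner; the interaction analyses already promised can examine this. The cost is one extra model term and a less favourable power figure for the partner-support coefficient. No additional data are needed.
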